### Outcomes

Primary outcomes:

The risk for persistent pain or pain worsening to a clinically important extent, using the risk stratification tool (combined clinical QST and CAP).Sensitivity and specificity of the risk stratification tool to identify people at risk of persistent and/or worsening pain.

Secondary outcomes:

External validity of the risk stratification tool against laboratory QST and validated questionnaires addressing central sensitisation-related characteristics.Internal validity of the risk stratification tool.Pain prognosis: Prediction of pain at 12 weeks by the risk stratification tool, CAP and clinical QST separately.Mechanistic underpinning: Investigate, according to the assessments outlined, which pain mechanisms contribute to risk levels identified using the risk stratification tool.Acceptability and feasibility of the risk stratification tool by patients, healthcare professionals (HCPs) and researchers within both research and clinical environments.Refinement of the risk stratification tool by patients, HCPs and researchers.Inter-rater and intrarater reliability of the risk stratification tool.

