Patient-centred outcomes will assess pain severity (Numerical Rating Scale^82^), quality (McGill^83^) and periodicity (pain diaries^84 85^), disability (Health Assessment Questionnaire^86^) and global quality of life (36-item Short Form Survey^87^). Potential confounders will also be included in the questionnaire, including demographics (age, sex, ethnicity, social deprivation,^88^ amenorrhea status), comorbidities (Rheumatic Disease Comorbidity Index^89^). Regular and current medication used will be classified as analgesic (subclassified: paracetamol, Non-steroidal anti-inflammatory drugs, anti-neuropathic (antidepressant, anti-convulsive), strong/weak opioid, other).

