### Sample size

A sample size of 250 participants at baseline, with an anticipated 200 individuals completing the follow-up questionnaires, accounting for 20% attrition.^92^ Provides additional statistical power and robustness to detect differences, allowing for more precise estimates of interactions and better management of potential missing data, therefore enhancing the validity of our findings.

Rasch measurement theory (RMT) to determine the structural validity of the risk stratification tool assumes that item calibrations lie within ±½ logit of stable values within a 99% CI, resulting in an overall sample size between 108 and 243, from best to poor targeting.^93 94^ This aligns with the Consensus-based Standards for the selection of health Measurement Instruments recommendations RMT analysis.^95^

Pain profiles will be identified irrespective of condition, using multivariate models with 5 covariates, 95% power and an effect size of 0.5 would require 236 individuals to complete baseline assessments.^51^ For longitudinal modelling, assuming a correlation coefficient of 0.15 with 12-week pain, 164 participants with α=0.05 and 95% power.

Interviews will be conducted until theoretical saturation, the point at which additional data do not reveal any new themes that achieve conceptual depth.^96^ It is anticipated that 27 interviews will be conducted with participants and 22 HCPs and researchers (table 2).

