### Data analysis

Pain profiling will be undertaken irrespective of condition. Multivariate modelling (principal component analysis, cluster analysis or latent class analysis) to identify distinct pain patterns.Between-group comparisons (eg, independent T-tests, Mann-Whitney U) will explore between pain profile comparisons.Associations between pain profiles and clinical outcomes (eg, pain intensity, pain-related worrying, disability, quality of life) will be examined.Sensitivity analysis will be conducted between diagnostic groups and between matched samples.We believe that QST will identify somatosensory pain profiles, while CAP will identify psychological hypervigilance pain profiles, each associated with augmented central pain processing. Using the pain profiles combined with pain at 12 weeks, we will identify any relationship between potential augmented central pain processing and pain prognosis at 12 weeks (eg, persistent/worsening pain, pain>patient acceptable symptom state), informed by patterns of pain over 12 weeks and knowledge.Pain prognosis: Bivariable correlations will identify and permit comparison between baseline factors significantly associated with 3-month pain prognosis. Separate multivariable models will determine whether the CAP questionnaire, clinical QST or laboratory QST can increase prognostic precision beyond other clinical and demographic variables significantly associated with pain prognosis. Multivariable modelling will define whether and which combination of the CAP questionnaire and QST importantly improves prognostic determination. The proportion of the prognosis explained by each and by both the CAP questionnaire and clinical or laboratory QST will be determined.The reliability and validity of the stratification tool (combined CAP and clinical QST) will be tested across the study population, with sensitivity analysis conducted across the diagnostic groups, age, sex, social and ethnic strata.Test–retest reliability will be assessed using intraclass correlation between repeated CAP questionnaires and between two raters for simplified clinical QST.RMT, Cronbach’s alpha and confirmatory factor analysis will evaluate internal validity, consistency and factor structure. If multiple constructs with significant residual values exist, this will be further explored using principal component analysis of residuals, the eigenvalue criterion, residual correlations and theoretical understanding.Correlation analysis will assess external validity against self-reported questionnaires and laboratory QST.Mechanistic underpinning: The dataset will be randomly divided into development and validation sets. Exploratory and confirmatory factor analyses will determine whether there are subgroups of the population for whom the stratification tools function differently. Correlations between CAP scores and clinical and laboratory QST indices of augmented central pain processing will be identified. Bivariate and multivariable models will ascertain whether associations may be explained by one or more characteristics linked to maladaptive pain processing (sleep disturbance, fatigue, anxiety, depression, cognitive impact, catastrophising).Relevance to patient-centred outcomes: Bivariate associations between CAP or QST and patient-reported outcome measures scores will be determined through linear regression. The proportion of participant-reported pain or other patient-reported outcome measures explained by CAP scores, clinical and/or laboratory QST measures, will be identified as R^2^ in multivariable regression.Qualitative data will be analysed using reflexive thematic analysis following the stages outlined by Braun and Clarke.^97^ A reflexive journal will be kept throughout the data collection process. Data will be coded inductively primarily, while also being informed by the Normalisation Process Theory^90 91^ commonly used to support evaluation in health interventions and inform the tool’s theoretical acceptability and feasibility. A ‘critical friend’^98^ will code a sample of transcripts independently until consensus is reached. After the consensus is reached, all remaining transcripts will be coded. NVivo V.15 will assist in managing, analysing, and visualising the qualitative data set. A thematic map may also visually represent the main themes developed.

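### The primary outcomes need a yes/no pain status, the longitudinal sample size uses a correlation with 12-week pain, and the plan does not fix which scale the prognostic models use

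*Protocol article*

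**What the plan says.** **Outcomes.** The first primary outcome is "The risk for persistent pain or pain worsening to a clinically important extent, using the risk stratification tool (combined clinical QST and CAP". The second is "Sensitivity and specificity of the risk stratification tool to identify people at risk of persistent and/or worsening pain". Among the secondary outcomes stands "Pain prognosis: Prediction of pain at 12 weeks by the risk stratification tool, CAP and clinical QST separately", with no cut named.

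**Objectives.** The ability of clinical QST and CAP, alone or combined, is to be judged by prediction of persistent or worsening pain at 6 and 12 weeks. Their contribution alongside other variables is judged by the same status at 12 weeks. Both aims appear under the primary and again under the secondary objectives.

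**Experimental procedures.** "Patient-centred outcomes will assess pain severity (Numerical Rating Scale"; the questionnaires that carry this scale are completed at baseline, 6 and 12 weeks. The eligibility criterion describes pain from 0 to 10.

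**Sample size.** 250 participants at baseline, 200 expected to complete follow-up, and "For longitudinal modelling, assuming a correlation coefficient of 0.15 with 12-week pain, 164 participants with α=0.05 and 95% power". No event share, sensitivity, specificity or area under the curve is given.

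**Data analysis.** The pain-profiling item ends by referring to "pain prognosis at 12 weeks (eg, persistent/worsening pain, pain>patient acceptable symptom state". The item on pain prognosis then plans bivariable correlations and multivariable models, and says "Multivariable modelling will define whether and which combination of the CAP questionnaire and QST importantly improves prognostic determination". It also promises the proportion of prognosis explained. It does not say whether prognosis there is pain on its scale or a yes/no status.

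**The concern.** The central question is whether the combined tool predicts better than CAP or clinical QST alone, and the one effect size stated for longitudinal modelling is small (r = 0.15). The objectives and primary outcomes frame prognosis as a status that a participant has or does not have. The sample size treats it as a quantity that correlates with a predictor. The analysis text leaves both readings open.

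If the comparisons are run on the status, graded pain scores are reduced to two classes. Participants just either side of the boundary are treated as different, and those far apart on the same side as alike. A real association is then easier to miss, and chance weighs more in the choice of tool components. On either reading, the Sample size section gives no power or precision figure for the two primary outcomes.

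**Working it through.** **Inputs from the protocol (Sample size).** r = 0.15, alpha = 0.05, stated power 95%, stated N = 164, expected completers 200 (250 × 0.8).

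**Assumptions.** Two-sided test, because sidedness is not stated. One predictor and pain roughly bivariate normal. The status is a simple cut of 12-week pain. The share with the outcome is not in the protocol, so 50% to 90% is shown; a share p and a share 1 − p give the same result.

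**1. The plan's own figure.** For one correlation, N = ((z₀.₉₇₅ + z₀.₉₅) / atanh r)² + 3, with atanh(0.15) = 0.1511.

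- N = ((1.960 + 1.645) / 0.1511)² + 3 ≈ 572 (477 if one-sided), so 164 is not reproduced.
- Power = Φ(atanh(r) × √(N − 3) − 1.960).
- At 164: Φ(0.1511 × 12.69 − 1.960) = Φ(−0.042) = 48.3%.
- At 200: Φ(0.1511 × 14.04 − 1.960) = Φ(0.161) = 56.4%.
- 164 at 95% power corresponds to r of about 0.277.
- Reading 0.15 as Cohen's f² gives 160 with 8 predictors and 166 with 9, but the protocol states neither that measure nor that number of predictors.

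**2. Effect of a cut.** Cutting pain so that a share p has the outcome multiplies the correlation by a = φ(z_p) / √(p(1 − p)). The effective sample is N × a². For p = 0.5 and N = 200: a = 0.798, the correlation becomes 0.1197, and power is Φ(0.1203 × 14.04 − 1.960) = Φ(−0.272) = 39.3%.

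| Share with outcome | a | Power, N = 200 | Loss from 56.4% (points) | Effective N of 200 |
|---|---|---|---|---|
| 50% | 0.798 | 39.3% | 17.1 | 127 |
| 70% | 0.759 | 36.1% | 20.3 | 115 |
| 80% | 0.700 | 31.5% | 24.9 | 98 |
| 90% | 0.585 | 23.4% | 33.0 | 68 |

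A simulation with 20,000 replicates at N = 200 gave 56.4% uncut and 39.2% at an even split. Rounding pain to whole points from 0 to 10 cost about 1 point, so the loss comes from the cut and not from the coarseness of the scale.

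**3. How far the loss depends on N and r (even split).**

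- N = 164, r = 0.15: 48.3% to 33.2%, a loss of 15.1 points.
- N = 200, r = 0.25: 95% to 81%, about 14 points.
- N = 200, r = 0.277: 97.9% to 88.3%, 9.6 points.
- The loss does not fall steadily with r. At N = 200 and r = 0.20 it is Φ(0.2027 × 14.04 − 1.960) = 81.2% against Φ(0.1610 × 14.04 − 1.960) = 61.8%, or 19.4 points.

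**The case against.** The strongest reply is that the predictor analysis may already be what is wanted. The two yes/no examples belong to the pain-profiling item. The pain-prognosis item that follows names no cut, and its correlations and proportion explained fit full-scale pain at least as well. The secondary outcome on pain prognosis also speaks simply of pain at 12 weeks. This stands: a reader might infer that the plan commits its predictor models to a cut of 0-10 pain, and the text does not establish that. Against it, the Objectives word the comparison of CAP and clinical QST, alone or combined, as prediction of persistent or worsening pain, and nothing in the analysis item settles the matter.

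A second reply is that sensitivity and specificity require a yes/no status. That is correct, and it is why the status should be kept for them.

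Third, no cut is fixed. Worsening is a change from baseline, and the definition is to be informed by pain patterns over 12 weeks, so a single cut of one normal variable only approximates the planned status. A reader might also take 17 points as a general minimum. It is the minimum only for N = 200 and r = 0.15. Nor do these single-predictor figures measure power to show that QST adds to CAP.

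Finally, this is a condensed article, and model details may sit in an analysis plan that is not shown. That covers the model form. It does not cover the mismatch between the stated outcomes and the stated sizing, which is in the article itself.

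**Conclusion.** The point holds in a conditional form. The primary outcomes and prediction objectives rest on a yes/no status, the only longitudinal sizing input is a correlation with 12-week pain, and the scale of prognosis in the comparative models is left open. If the status is used there, power for one predictor at 200 completers and r = 0.15 drops from about 56% to about 39% at best, and to 23% to 36% for shares from 90% to 70%. This rests on a two-sided 5% test, approximate normality, a simple cut and an assumed outcome share.

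The documents do not support the stronger statement that the predictor analyses will lose 17 or more points.

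Keeping the full scale would not rescue the stated power. At r = 0.15 even the uncut analysis has about 48% at 164 and 56% at 200. That shortfall is larger than the loss from the cut at an even split. It is also a reason not to discard information that is already being collected.

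**What to change.** **Data analysis, pain prognosis item.** State that the comparisons of CAP, clinical QST, laboratory QST and their combination are made on the 12-week pain rating on its full scale, by linear or ordinal regression. Prespecify the baseline pain rating as a covariate and keep CAP and QST continuous. Keep the yes/no status for sensitivity and specificity, as the clinical read-out.

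**Sample size.** State that the correlation-based figure refers to the full-scale analysis and gives no power for the yes/no primary outcomes. Restate its power: about 48% at 164 and 56% at 200 for r = 0.15, two-sided. If 0.15 was meant as another effect measure, name it and give the number of predictors.

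**Cost.** Wording only, with no new data, visits or participants. Pain ratings are bounded, so an ordinal model or robust standard errors are needed. The full-scale result is a pain difference or proportion explained and must be translated into a risk for clinical use.

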### Experimental procedures

Participants will attend a single study visit that includes the new tool, patient-reported outcome measures, laboratory QST, and clinical assessments. They will be asked to wear an activity monitor for 1 week to evaluate the impact of sleep on pain. Pain will also be reported via SMS text messages weekly for 12 weeks. A subgroup of individuals will complete an additional CAP questionnaire and qualitative semistructured interviews within 1 week of their baseline visit. Patient-reported outcome measures (questionnaire booklet) will be repeated at 6 and 12 weeks. The CONSORT flow diagram (figure 1) outlines the participants’ journey. Participants may withdraw at any time without providing a reason, without prejudice to their medical care.

**Figure 1 F1:**
[figure not shown]
CONSORT (Consolidated Standards of Reporting Trials) participant flow diagram. CAP, Central Aspects of Pain; NHS, National Health Service; PIS, Participant Information Sheet; T0, time 0 (baseline); T1, time 1 (6 weeks); T2, time 2 (12 weeks).

The combined tool will include the CAP questionnaire and clinical QST modalities, replicating laboratory QST using low-cost equipment currently available within the UK National Health Service (NHS) (table 1). The CAP questionnaire^35 36 38 39^ has been selected because it was developed based on the current mechanistic understanding of augmented central pain processing and the potential patient-reported effects. CAP includes eight items strongly associated with QST in musculoskeletal pain.^38^ It displays excellent psychometric properties, is feasible, patient-acceptable and can predict pain prognosis in musculoskeletal conditions so far investigated.^35^,^3751^

**Table 1 T1:** Laboratory versus clinical QST assessments for pain hypersensitivity

Modality	Laboratory	Clinical
**Pressure Pain Detection Threshold (PPT**) **Protocol:** Pressure is increased at 50 kPa/s until the sensation of pressure changes to pain^53^ **Test sites:** non-dominant brachioradialis	**Equipment:** Pressure algometer (Algomed, Medoc) 1 cm^2^ tip	**Equipment:** Handheld dynamometer (Wagner Force Ten) 1 cm^2^ tip
**Temporal Summation of Pain** **Protocol:** apply single stimuli, apply 10 stimulations at 1/s and rate pain/sharpness after 1 and 10 **Test sites:** dominant brachioradialis	**Equipment:** Pinprick stimulator (256 mN pinprick)	**Equipment:** Von Frey Filament (256 mN)
**Conditioned Pain Modulation** **Protocol:** PPT is performed preconditioning and postconditioning. Conditioning: A blood pressure cuff will be inflated until the distal radial pulse cannot be palpated. Participants are then asked to squeeze a ball until pain reaches 4/10. **Test sites:** non-dominant brachioradialis	**Equipment:** Blood pressure cuff, pressure algometer (Algomed, Medoc)	**Equipment:** Blood pressure cuff, handheld dynamometer 1 cm^2^ tip (Wagner Force Ten)

QST, quantitative sensory testing.

QST will be assessed on the brachioradialis muscle belly 5 cm from the lateral epicondyle^52^ of the dominant (PPT, CPM) and non-dominant arm (TSP), and the volar forearm of the dominant arm (Heat Pain Threshold (HPT), Offset-analgesia) (figure 2). Each laboratory and clinical QST protocol test will be undertaken in a standardised order (PPT, TSP, CPM, HPT, then offset analgesia). The order of laboratory and clinical QST will be randomised to minimise the potential for sequential effects to confound comparisons between the two modalities. These measures have previously been well tolerated by individuals with musculoskeletal pain and will be conducted regardless of their pain status.

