Using the Advanced Pain Discovery Platform CPM protocol, PPT will be measured before and after a pain-conditioning stimulus. The unconditioned stimulus will be the average of three trials on the non-dominant brachioradialis muscle. A 15 cm wide pressure cuff on the dominant forearm will be inflated to occlude arterial blood flow. Participants will be asked to squeeze a stress ball until they indicate pain levels of 4/10 (0=no pain, 10=worst pain imaginable) due to ischaemic pain,^56^ at which point PPT is performed again before the cuff is released. The CPM effect will be calculated as the mean of three unconditioned PPT minus the conditioned PPT.^56^ Thus, negative values indicate an inhibitory CPM effect and positive values a facilitatory effect.^56^ To account for measurement error, the within-participant coefficient of variation (CoV) of the unconditioned PPT will be determined; only the CPM effect greater in magnitude than the CoV will be considered a true response.^57^

HPT will be assessed using a 6.6×4×4.4 cm probe (TCS II, QST.Labs, France) applied to the non-dominant volar forearm. To overcome adaptation or sensitisation, the forearm is divided into four zones (figure 2), with the probe moved from zone to zone between stimuli.^58^ The method of limits will be used to establish the heat thresholds. A computer-controlled heat stimulus will be applied, with the baseline temperature set at 32°C and increasing at a rate of 1°C/s to a maximum of 50°C.^57^ The participant will indicate using a handheld button when the sensation of heat changes to one of pain, at which point the test is stopped. HPT is calculated as the mean of three replicates taken 10 s apart. Lower HPT values indicate greater sensitivity to thermal pain.

Offset analgesia will be measured using a tonic heat stimulus train to the skin of the non-dominant volar forearm (figure 2). The study temperature will be individualised. Starting at baseline (32°C), the first temperature will be set to HPT for 10 s, then returned to baseline and increased by 1°C. The participant will continuously rate their pain on an electronic VAS (eVAS). When the eVAS reaches 50/100, the test will be stopped^58^ and the actual temperature recorded. Pain^50^ will be determined as the average of two trials separated by 1 min. To ensure the tonic heat stimulus is noxious for the offset analgesia protocol, the following rule will apply:

Pain^50^<45°C then tonic heat stimulus=Pain^50^+2°C.

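### The QST site paragraph gives the opposite test arm to Table 1 or the procedure text for all five arm-specific modalities, so the passages must be reconciled

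*Protocol article*

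**What the plan says.** The protocol article states the test arm for QST in three places, all under Experimental procedures.

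- **QST site paragraph (after Table 1).** The brachioradialis and volar forearm sites are assigned to sides as follows: "of the dominant (PPT, CPM) and non-dominant arm (TSP), and the volar forearm of the dominant arm (Heat Pain Threshold (HPT), Offset-analgesia".
- **Table 1.** The PPT row reads "until the sensation of pressure changes to pain^53^ Test sites: non-dominant brachioradialis". The TSP row reads "Test sites: dominant brachioradialis". The CPM row again gives the non-dominant brachioradialis.
- **Procedure paragraphs (after Figure 2).** For CPM, "The unconditioned stimulus will be the average of three trials on the non-dominant brachioradialis muscle". The next sentence gives the conditioning side: "A 15 cm wide pressure cuff on the dominant forearm will be inflated to occlude arterial blood flow". PPT is repeated while the cuff is still inflated. The HPT probe is "applied to the non-dominant volar forearm", and offset analgesia is placed on the same, non-dominant, side.

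The PPT and TSP procedure paragraphs name no arm. The Figure 2 legend names the muscle and forearm locations but no arm, so the text of the legend does not settle the matter.

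**The concern.** The test arm is an operative measurement instruction. The study is multisite and still recruiting, and it plans intraclass correlations between two raters for the simplified clinical QST and correlations of the tool with laboratory QST. If staff worked from different passages, the arm would vary for reasons unrelated to the participant's pain processing.

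CPM needs most care. The Introduction treats it as a proxy for descending modulatory control, and the effect is the mean unconditioned PPT minus the conditioned PPT. That reading is cleanest when the test stimulus is away from the conditioned limb. If the second PPT were taken on the limb under occlusion, any local effect of compression or ischaemia would sit inside the difference and could not be separated from descending modulation.

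**Working it through.** No calculation applies. The check sets the stated arms side by side.

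| Modality | QST site paragraph | Table 1 | Procedure paragraph | Conflict |
|---|---|---|---|---|
| PPT | dominant | non-dominant | no arm named | yes |
| TSP | non-dominant | dominant | no arm named | yes |
| CPM, test PPT | dominant | non-dominant | non-dominant | yes |
| CPM, cuff | not mentioned | arm not stated | dominant forearm | single statement |
| HPT | dominant | not listed | non-dominant | yes |
| Offset analgesia | dominant | not listed | non-dominant | yes |

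1. **Count.** The site paragraph is contradicted for 5 of 5 arm-specific modalities: three by Table 1 (PPT, TSP, CPM) and three by the procedure text (CPM, HPT, offset analgesia), with CPM in both sets (3 + 3 − 1 = 5). The tender point count uses bilateral sites and is not affected.

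2. **Which statements agree.** CPM is the only modality whose test arm is given in all three places. There, Table 1 and the procedure text agree and the site paragraph stands alone. For the other four modalities it is one statement against one.

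3. **CPM geometry.** Within the CPM procedure paragraph, the test PPT is on the non-dominant arm and the cuff on the dominant forearm, so they are on opposite limbs. Taking the test arm from the site paragraph (dominant) and the cuff arm from the procedure paragraph (dominant) puts both on one limb, with the second PPT taken under occlusion. This needs the two passages to be mixed.

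4. **Which analyses can be touched.** PPT, TSP and CPM have both laboratory and clinical versions and are the clinical QST that two raters will assess. HPT and offset analgesia are laboratory-only, so they enter neither the inter-rater correlation nor a paired same-modality comparison. Both the site paragraph and Table 1 assign the arm by modality, not by version. Whichever is followed consistently, the laboratory and clinical versions fall on the same arm of the same person at a single visit. Arm differences enter within-person pairs only if two raters, or the two versions, followed different passages. If whole sites differed, the arm would instead vary between participants.

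5. **Size.** The documents give no dominant-versus-non-dominant difference for any modality and no effect of local occlusion on PPT, so no bias can be computed.

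**The case against.** The strongest reply is that this is a drafting slip. The site paragraph is a one-sentence overview whose sides are the exact mirror of the detailed text, which looks like one swapped pair of words. The CPM procedure paragraph is coherent in itself, agrees with Table 1 on the test arm and names the platform protocol it follows. The article also condenses an ethics-approved protocol (version 1.0, cited under Ethics and dissemination) that is not shown, and sites may well work from that. All of this is plausible, and it limits what can be claimed. It does not remove the contradiction: the article commits itself to both arms, and anyone applying the tool from it cannot tell which was meant.

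Three stronger readings are tempting, and the documents do not support them:

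- A reader might infer that every CPM value is being taken on the cuffed limb. No passage describes that procedure; it arises only by joining two passages and setting aside the test site given in the sentence just before the cuff.
- A reader might infer that a third of the risk tool loses its meaning. The Abstract lists clinical QST (PPT, TSP, CPM), tender point count and the CAP questionnaire, so CPM is one of three clinical QST modalities within a larger tool.
- A reader might infer that reliability and validity are compromised for all five modalities, or that participants have been tested wrongly. The paired comparisons concern three modalities at most, and nothing in the article shows a failure in conduct.

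**Conclusion.** The article is wrong as written: for each of the five arm-specific QST modalities, at least one stated test arm must be incorrect. For CPM the site paragraph is the outlier against two concordant statements; for the others, the text alone does not show which statement is the error.

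The consequence for the data is conditional. It requires that raters, versions or sites actually followed different passages or, for the CPM interpretation problem, that the site paragraph's test arm was used with the procedure text's cuff arm. That a same-limb measurement would confound local effects with descending modulation is measurement reasoning, not a figure from the documents. No sample-size or power figure depends on this point. It deserves correction now because it is a live instruction in a study expected to run to April 2027, and any inconsistency can still be found and stopped.

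**What to change.** - **Reconcile the text.** Bring the QST site paragraph, Table 1 and the procedure paragraphs into one statement giving, for each modality, the test arm and site and, for CPM, the cuff arm. It should be identical for laboratory and clinical versions and for all sites and raters, and should match the approved protocol and the working instructions at sites.
- **Confirm practice.** Recruitment began in October 2024, so check source records for the arm used. If practice was uniform, say so and stop there.
- **Conditional handling.** Only if some CPM tests were done on the cuffed arm, flag those values and report CPM results with and without them.

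The cost is a text correction, a short note to sites and a source-record check. No new procedure, visit or participant is needed.
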